[19] will also be utilized to obtain more objective and quantitative results. This trial aims to confirm the effectiveness and safety of acupuncture in the treatment of adolescent myopia.

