### Recruitment strategies

The subjects will be informed of the details regarding the trial plan and those who voluntarily participate in the trial will receive free ophthalmologic examinations. Following optometric evaluation, these subjects will receive the highest discount (30% off) on glasses. Subjects in the experimental group will receive a 50% discount on acupuncture treatment. All subjects who receive a follow-up eye exam will not pay a fee and will be permitted to be fast-tracked. The subjects who will be included in the experimental group will receive treatment any time between 10:00 and 19:00 (Beijing time). If adverse events occur during treatment, the treatment will be immediately terminated, and help will be obtained from the emergency department. According to the specific condition which occurs after treatment, a consultation involving at least three experts will be carried out to decide whether or not to continue the clinical trial. Subject compliance will be determined based on whether or not the subject receives due treatment. The researchers will ensure that the subjects in the experimental group fully understand the importance of regular acupuncture and compliance. During the observation period, the use of drugs or other therapies to treat mild-to-moderate myopia will be prohibited.

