### Intervention

Subjects in the acupuncture group will wear SVLs. Acupuncture will be performed at five acupuncture points (bilateral Cuanzhu (BL2), Tongziliao (GB1), Sibai (ST2), Muchuang (GB16), and Hegu (LI4), see Figures 
2 and
3). Alcohol (75%) will be used to routinely disinfect the local skin at the acupuncture points and 0.25 mm × 0.4 mm disposable sterile acupuncture needles (Suzhou Acupuncture & Moxibustion Appliance Co., Ltd., Suzhou, China) will be used at acupuncture points Sibai and Hegu to a depth of 0.5 to 1.0 cm. After achieving *de-qi* (Subjects have a feeling of soreness, fullness, aching, heaviness at and around the acupoints), the needle will be held in position for 20 minutes. Cuanzhu will be acupunctured to a depth of 0.3 to 0.5 cm. Tongziliao and Muchuang will be acupunctured to a depth of 0.1 to 0.3 cm. After achieving *de-qi*, the needle will be held in position for 20 minutes. Acupuncture will be carried out once a day between 10:00 and 19:00 (Beijing time). One cycle of treatment will last for nine days, followed by one day of no treatment. Six cycles of treatment will be undertaken continuously for a total of 60 days. The acupuncturist in this study, a physician with 18 years of experience in clinical acupuncture, will not participate in objective examinations, such as visual acuity. Subjects in the control group will wear SVLs without any other treatment affecting visual acuity. Observations will be carried out for two consecutive months.

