### Harms

In the proposed study, adverse events, included bleeding, hematoma formation, fainting, severe pain, and local infection, will be reported
[26]. If adverse events occur during the observation period, details of these adverse effects will be recorded in the CRFs.

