### Statistical analysis

All statistical analyses will be performed using SPSS 17.0 statistics software. For quantitative data, the distribution pattern and homogeneity of variance will be examined. If there is a symmetric distribution, the mean (M) ± standard deviation will be used for statistical description, otherwise the M interquartile range (IQR) will be used to describe the trend of concentration and amount of scatter. If this condition is met, the Student's t-test will be used to compare the differences between the quantitative indices between the groups, otherwise the Wilcoxon rank-sum test will be used. For categorical data (binary classification and multiple classification), the composition ratio will be used for statistical description. Based on the observation of a theoretical frequency distribution, the χ^2^ or Fisher's exact test will be used, depending on the specific situation. The ranked data will be analyzed using the Wilcoxon rank-sum test.

Primary and secondary outcomes will be analyzed by the superiority test in accordance with the principle of intention-to-treat, using Per Protocol Set (PPS) and Full Analysis Set (FAS) datasets. The indices of safety evaluation will be analyzed using the Save Set (SS) dataset. The significance level in this study will be set at α = 0.05, and the one-sided test will be used. The detailed statistical analytical methods for primary and secondary outcomes and baseline data are shown in Table 
2 (variables, measures, and methods of analysis).

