**Table 2 Tab2:** **Variables, measures, and methods of analysis**

Variable/outcome	Hypothesis	Outcome measure	Methods of analysis
1) Primary	Intervention improved outcome from baseline to 7 days	Adherence% (>80%) [binary]	
Diopter	Diopter reduced or increased after treatment	Diopter [continuous]	t-test (rank-sum test) or repeated measurement
2) Secondary	Intervention improved outcome from baseline to 7 days	Adherence% (>80%) [binary]	
Visual acuity	Visual acuity did not increase or decrease after treatment	Visual acuity changes [continuous]	t-test (rank-sum test) or repeated measurement
Axial length	Axial length was not increased	Axial length changes [continuous]	t-test (rank-sum test) or repeated measurement
Lens thickness	Lens thickness was not increased	Lens thickness changes [continuous]	t-test (rank-sum test) or repeated measurement
Ciliary body thickness	Ciliary body thickness was not increased	Ciliary body thickness changes [continuous]	t-test (rank-sum test) or repeated measurement
Eye symptoms and systemic symptoms	No adverse symptoms	No adverse symptoms	Chi-squared test or Fisher’s exact test
Compliance	Compliance	Cure rate [binary]	Chi-squared test or Fisher’s exact test
Combination therapy/treatment	Improvement occurred	Whether other drugs were used during treatment [binary]	Chi-squared test or Fisher’s exact test
Adverse event	Improvement occurred	Presence of drug-related adverse event [binary]	Chi-squared test or Fisher’s exact test
3) Baseline analyses:		Adherence% (>80%) [continuous]	
Age		CRF [continuous]	t-test (rank-sum test)
Weight and height		CRF [continuous]	t-test (rank-sum test)
Female versus male		CRF [binary]	Chi-squared test or Fisher’s exact test
Race		CRF [more categories]	Chi-squared test or rank-sum test
Birth weight		CRF [continuous]	t-test (rank-sum test)
Preterm children		CRF [binary]	Chi-squared test or Fisher’s exact test
Parental myopia or not		CRF [binary]	Chi-squared test or Fisher’s exact test
Sibling myopia or not		CRF [binary]	Chi-squared test or Fisher’s exact test
Daily close reading time		CRF [continuous]	t-test (rank-sum test)
Outdoor time		CRF [continuous]	t-test (rank-sum test)
Eye exercises every day or not		CRF [binary]	Chi-squared test or Fisher’s exact test
Daily sleep time		CRF [continuous]	t-test (rank-sum test)
Room light conditions		CRF [binary]	Chi-squared test or Fisher’s exact test
Poor reading habits		CRF [more categories]	Chi-squared test or rank-sum test

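### Table 2 measures adverse events as drug-related and compliance as a cure rate; neither fits a trial of needling against lenses, and both contradict the protocol's own text

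*Protocol article*

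**What the plan says.** Under Statistical analysis the article states: "The detailed statistical analytical methods for primary and secondary outcomes and baseline data are shown in Table" 2. Two rows of that table matter here.

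- **Adverse event.** The outcome measure is "Presence of drug-related adverse event [binary", the hypothesis is that improvement occurred, and the method is a chi-squared or Fisher's exact test.
- **Compliance.** The outcome measure is "Cure rate [binary", with the same choice of tests.

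The primary and secondary heading rows of the table also carry "Adherence% (>80%) [binary", with no method of analysis beside it.

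Elsewhere the article describes the same items differently. The Harms section says that "adverse events, included bleeding, hematoma formation, fainting, severe pain, and local infection, will be reported", with details entered in the case report form. Recruitment strategies says: "Subject compliance will be determined based on whether or not the subject receives due treatment". The Background gives safety equal standing with efficacy: "This trial aims to confirm the effectiveness and safety of acupuncture".

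**The concern.** Table 2 is the only place in the article that ties each outcome to a measure and a test, so a statistician would work from it. The statistician is also to be blinded to allocation, which leaves little room to repair a measure informally once data arrive.

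A drug-related event is the wrong category where the arms differ by needling. A cure rate is an efficacy idea, and it does not say whether a child attended for treatment. If the rows were followed to the letter, the tabulated safety comparison would not address the harms that acupuncture can cause in children aged seven to 12 needled around the eye, and an undefined cure rate would appear in the results under the name of compliance.

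**Working it through.** The check is mainly a comparison of sections, with a little arithmetic at the end.

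**1. Is either randomized treatment a drug?** No. The Intervention section says "Acupuncture will be performed at five acupuncture points", with lenses; controls wear lenses only. The drugs that the protocol itself gives are examination eye drops: cyclopentolate for refraction (Primary outcome) and oxybuprocaine for the ultrasound measurements (Secondary outcomes). Table 1 schedules these examinations without distinguishing the arms. A drug-related event, read literally, is therefore mostly a reaction to examination drops, which does not reflect the randomized difference.

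**2. Does the row agree with the rest of the text on harms?** No.

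| Place | What it covers |
|---|---|
| Harms | Needling-type events, reported and recorded, with no condition about drugs |
| Withdrawal conditions | Full analysis of adverse reactions to acupuncture |
| Excluded cases | Anyone who had a treatment session stays in the adverse-reaction analysis |
| Table 1 | Adverse events and skin damage, during treatment and at each later visit |
| Table 2, adverse-event row | Drug-related events only |

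**3. Does another Table 2 row fill the gap?** Only in part. The row for eye and systemic symptoms has no drug condition and may catch fainting or pain. It does not clearly cover local bleeding, hematoma or infection. Skin damage is collected in Table 1 but has no row in Table 2.

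**4. Does the hypothesis make sense?** No. That improvement occurred is not a hypothesis about the presence of an adverse event.

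**5. Does the compliance row agree with the text?** No. Recruitment strategies ties compliance to treatment received; the row names a cure rate, and no section defines cure. The row also specifies a between-group test, although controls have no sessions to attend.

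**6. Arithmetic for a usable compliance measure.** The Intervention section gives six cycles of nine treatment days: 6 × 9 = 54 sessions. If the table's 80% cut-off refers to sessions, 0.80 × 54 = 43.2. More than 80% then means at least 44 sessions (44/54 = 81.5%; 43/54 = 79.6%).

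**7. Illustration of size (hypothetical).** The protocol gives no expected rate of needling harm. Suppose 5 of the 50 acupuncture children had a hematoma and no child reacted to the eye drops. Read literally, the row would show 0/50, with an exact two-sided 95% upper limit of 1 − 0.025^(1/50) = 7.1%. The actual figure would be 5/50 = 10%, exact 95% interval 3.3% to 21.8%. The count of 5 is invented, and the contrast applies to this one row only.

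**The case against.** The strongest reply is that these are slips of wording. No randomized treatment is a drug and the text speaks of reactions to acupuncture, so drug-related plausibly stands for treatment-related. Event definitions and rules for causality are also commonly left to a full protocol or analysis plan.

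Part of this stands. The intended meaning may well be treatment-related, and no loss of harms data is shown. But the article does not leave the measure open. It states one, in the table it relies on for detailed methods, and that measure conflicts with its own text. A later analysis plan built on the table would inherit the conflict.

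Two stronger readings are tempting, and the documents support neither.

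- **A reader might infer that needling harms will be counted as zero.** They are recorded, reported and meant to be analyzed under Harms, Withdrawal conditions and Excluded cases. The symptoms row is a second safety variable. Even the adverse-event row need not read zero, because reactions to the examination drops are possible.
- **A reader might infer that compliance is never measured.** Recruitment strategies says how it is determined, and Table 2 itself holds adherence entries with an 80% cut-off. What is wrong is the measure in the compliance row.

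**Conclusion.** The point holds as a contradiction in the analysis specification. The adverse-event row names a measure that, taken literally, omits the harms most relevant to the intervention; the compliance row names an undefined efficacy measure.

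The consequence is limited to those two rows. It does not touch the primary efficacy comparison or the collection of safety data. It should still be corrected before analysis, because safety is a stated aim and this is the table's only row for adverse events as such. How far a reported rate would shift cannot be derived from the protocol.

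The conclusion rests on reading Table 2 as the working specification, as the Statistical analysis section says. The threshold of 44 sessions rests on the further assumption that the 80% refers to sessions received, which the article does not state.

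**What to change.** Reword two rows of Table 2.

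- **Adverse events.** Make the measure the number of children with at least one adverse event of any cause, compared between arms in the safety set. Add acupuncture-related events, including each type listed under Harms, described in the acupuncture arm. Delete the hypothesis that improvement occurred. Because Excluded cases words inclusion in terms of treatment sessions, say how controls enter the safety set.
- **Compliance.** Replace the cure rate with the proportion of the 54 scheduled sessions received, described in the acupuncture arm only and not tested between arms. State whether the existing adherence cut-off of more than 80% applies to it; if so, it means at least 44 sessions.

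The cost is small. Adverse events already go into the case report form. The article does not say that session attendance does, so that should be confirmed. Trial status reports six participants recruited, so the change can precede any results. If it is treated as a major change of analytical method, the notifications under Protocol amendments and confidentiality apply.

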### Monitoring

In the proposed study, a Data Monitoring Committee (DMC) will be installed; the quality control office of the entire project will be set up in DMC. A quality control team will also be set up and a person-in-charge will be appointed (members are the researchers, consisting of personnel from the Ethics Committee, statistical analysis personnel, and clinical professionals (five people in total)) to identify problems in the project implementation process in a timely manner and to implement the corresponding countermeasures. The collected data will be examined, and the researchers will be supervised to control bias.

### Protocol amendments and confidentiality

Notification of major modifications to the project (inclusion criteria, outcomes, and analytical method) will be provided to the Ethics Committee, subjects, register, and publisher. The researchers promise to keep the information and technology involved in the files confidential. The personal information on the subjects will be strictly confidential, and not disclosed under any circumstances. Moreover, a confidentiality agreement will be signed.

### Ancillary and post-trial care

When emergencies or adverse reactions are observed, the researchers will carry out the corresponding countermeasures according to the symptoms to ensure the safety of the subjects. The results of the treatment administered will be reviewed by the project director. The treatment and the results of treatment will be recorded in detail in the CRFs, which will later be signed. If adverse reactions related to treatment occur and need treatment, the research team will meet the costs of treatment according to relevant regulations. Patients who experience adverse effects are given economic compensation.

## Discussion

Traditional Chinese medicine theory states that the ‘meridian is the channel through which *qi* and blood circulate. An acupoint is the site where the *qi* of the viscera is transferred and concentrated’
[29, 30]; the meridian is the pathway for the body surface to connect and interact with the internal organs; and the acupuncture point is a specific point on the meridians, forming a special functional relationship with the corresponding viscera and the related surface structure through the meridians. Stimulation of the acupuncture point can have a specific treatment effect. Therefore, traditional Chinese medicine purports that ‘the meridian circulation is closely related to the amount of meridian *qi* concentrated’
[31]. Acupuncture treatment has a clinical effect, and acts on specific meridians and collaterals and specific acupuncture points
[31]. Some studies suggested that acupuncture at visual-related acupoints could modulate optical physiology
[32]. Acupuncture points are specific, but in a relative sense
[30]. Therefore, in the proposed study the local points (Cuanzhu, Tongziliao, Sibai, Muchuang, and Hegu) will be acupunctured simultaneously, and the clinical efficacy of acupuncture treatment in adolescent mild-to-moderate myopia will be determined.

The advantages of the proposed study will be four-fold. Firstly, Cuanzhu, Tongziliao, Sibai, Muchuang, and Hegu will be acupunctured to study the specific efficacy and safety of acupuncture in adolescent mild-to-moderate myopia. Secondly, the acupuncturist involved in the proposed study will have more than 10 years of experience in clinical acupuncture. The acupuncture procedure in all subjects in the experimental group will be carried out by the acupuncturist, which will ensure consistency of acupuncture treatment. Thirdly, the subjects will mainly be children from a primary school near the hospital, which will help to ensure regular follow-up visits and examinations of the subjects. Fourthly, previous clinical experience has shown that acupuncture treatment of adolescent simple myopia has almost no side effects.

The limitations of the proposed study are three-fold. Firstly, due to a limited budget, the proposed study will not be a multicenter trial, which will influence the external validity of the conclusions. Secondly, common fake acupuncture methods include neighboring sham acupuncture, non-specific site acupuncture, superficial acupuncture, minimal acupuncture, and a placebo needle; all of these methods could be used as a control, but with obvious deficiencies
[33]. Therefore, in the proposed study a sham acupuncture group will not be included. Quantitative, objective indices, such as diopter, AL, lens thickness, and ciliary body thickness will be selected as the outcomes to evaluate the clinical efficacy at a reduced bias. Thirdly, in the proposed study, 100 cases will be included and followed up on for six months. To prevent bias caused by loss-to-follow-up, the following measures will be adopted: first, the subjects will be from an elementary school near the hospital. Second, before the subjects are entered into the proposed study, their guardians will fully understood the specific requirements of the follow-up schedule, as outlined in the informed consent form. Once the subjects are included in the study, communication with the guardians will be strengthened by phone calls or email. The subjects will be informed of the follow-up examination time and place in advance. The subjects will receive the follow-up examination immediately after arriving.

This will be a randomized, parallel controlled trial, and it is anticipated that acupuncture treatment of adolescent mild-to-moderate myopia will be shown to be safe and effective. The proposed study will demonstrate the specificity of the meridians and acupuncture points and provide evidence-based medical evidence on the use of acupuncture to treat myopia.

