**Methods/Design:**

A randomized, parallel, single-center, assessor- and statistician-blinded, controlled clinical trial will be performed. A total of 100 teenagers, between seven and 12 years of age, with mild-to-moderate myopia and spherical lenses <-6.00 D and cylindrical lenses <-1.50 D will be selected from the Xinjiang Uygur Autonomous Region Institute of Traditional Chinese Medicine, a grade III level A teaching hospital in Urumqi, Xinjiang, China (Xinjiang Medical University Affiliated Hospital of Traditional Medicine). The subjects will be randomly assigned to two different groups (control and acupuncture groups), each group containing 50 subjects. The subjects in both groups wear single-vision corrective lenses. In the acupuncture group, acupuncture will be performed daily for nine consecutive days on five points (bilateral Cuanzhu, Tongziliao, Sibai, Muchuang, and Hegu), followed by no treatment for one day. Six cycles of treatment will be undertaken continuously for a total of 60 days. Following 60 days of treatment, a follow-up period of six months will be included. The primary outcome will be diopter determination. The secondary outcomes will include distance visual acuity, axial length, lens thickness, ciliary body thickness, and subjective symptoms of the eyes and entire body. The main time points for the evaluation of clinical efficacy will be the first, third, and sixth months after treatment.

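### The Discussion says the trial will show that acupuncture points and meridians are specific, but comparing lenses plus needling with lenses alone cannot show this at any sample size

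*Protocol article*

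**What the plan says.** The closing paragraph of the Discussion announces a result without qualification: "The proposed study will demonstrate the specificity of the meridians and acupuncture points".

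The design is given in four places:

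- Abstract, Methods/Design: "The subjects will be randomly assigned to two different groups (control and acupuncture groups), each group containing 50 subjects".
- Intervention, acupuncture arm: "Subjects in the acupuncture group will wear SVLs". These children also receive needling. The Discussion adds that "the local points (Cuanzhu, Tongziliao, Sibai, Muchuang, and Hegu) will be acupunctured simultaneously".
- Intervention, control arm: "Subjects in the control group will wear SVLs without any other treatment affecting visual acuity".
- Discussion, limitations: after naming several sham techniques and noting their deficiencies, the article says that "in the proposed study a sham acupuncture group will not be included".

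The aim under Study design is narrower than the closing claim. It is the clinical efficacy of acupuncture at the five named points, and specificity of points or meridians is not mentioned.

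**The concern.** To say that points or meridians are specific is to say that needling these locations does something that needling elsewhere, or a convincing imitation, does not. That is a comparison between two kinds of needling, and this trial has only one kind, set against none.

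What is at stake is the conclusion that a positive trial may carry. A published protocol sets out in advance what a favourable result will be taken to mean. If this sentence stands, a difference between the arms could be cited as evidence for point and meridian specificity, although the same difference would be expected if location made no contribution and needling in general, or the treatment setting, accounted for all of it.

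**Working it through.** The article gives no figure for specificity to reproduce. The check is to list what each arm receives and ask which contrasts the arms allow.

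**Step 1: treatment exposure.** Intervention gives nine treatment days and one rest day per cycle, for six cycles.

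- Course length: 6 × (9 + 1) = 60 days, which agrees with the article's 60 days.
- Sessions per child in the acupuncture arm: 6 × 9 = 54.
- Matching sessions described for the control arm: none. These children are observed over the same two months.

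**Step 2: components in each arm.**

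| Component | Acupuncture arm | Control arm |
|---|---|---|
| Single-vision lenses | yes | yes |
| Needling at the five chosen points (location-specific part, *s*) | yes | no |
| Needling as such, at any site (*g*) | yes | no |
| Expectation and 54 treatment contacts (*c*) | yes | no |

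**Step 3: the available contrast.** Two arms give one between-group difference. Lenses cancel, and what remains is

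Δ = *s* + *g* + *c*

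(written additively for simplicity; interactions would only make the parts harder to separate). This is one equation with three unknowns. The case *s* = Δ with *g* + *c* = 0 and the case *s* = 0 with *g* + *c* = Δ predict the same difference between the arms. The first is full specificity and the second is none.

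**Step 4: does sample size help?** The standard error of Δ with *n* per arm is S × √(2/*n*). Taking the article's S = 0.25 and *n* = 50 purely as an illustration, this is 0.25 × √(2/50) = 0.25 × 0.20 = 0.05. A larger *n* brings the standard error towards zero, so Δ becomes known precisely. It adds no second equation, and *s* stays undetermined.

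**Step 5: is there a comparison within the acupuncture arm?** No. Every child in that arm is assigned all five points together, so no point or meridian is left out for some children and used for others.

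**Step 6: the Discussion against itself.** The limitations paragraph says there is no sham group. The next paragraph promises a result that needs a sham or other-point comparator. Both cannot stand.

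**The case against.** The strongest reply is that the sentence governs nothing. It is a closing remark in the Discussion. The aim, the outcomes, the sample-size inputs, the analysis section and the hypotheses in Table 2 do not concern specificity, and deleting the sentence would leave arms, data and tests as they are. This is true. It limits the weight of the point and makes the remedy cheap, but it does not make the sentence correct.

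A second reply is that the missing sham is already disclosed and is offset by objective outcomes and by blinding of the assessor and statistician. The disclosure is real, though it does not name contact or expectation. Objective measures and blinded assessment reduce measurement bias; they do not separate *s* from *g* and *c*. Expectation is not fully excluded either, since the primary measurement includes a subjective refraction stage and visual acuity depends on the child's responses.

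A third reply is that an article condenses a fuller protocol. That would answer an omission. Here the article makes a positive claim that its own design rules out.

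Several stronger readings are tempting, and the document does not support them:

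- *The phrase in the Discussion's list of advantages, "to study the specific efficacy and safety of acupuncture in adolescent mild-to-moderate myopia", is a second overclaim.* It can simply mean efficacy in this particular condition. Nothing there defines it as efficacy beyond sham, and the Discussion elsewhere calls point specificity relative.
- *Daily attendance changes the children's near-work and so contributes to the difference.* The article does not suggest this. It lists close-reading and outdoor time as baseline data only.
- *A positive result will be reported as proof of specificity.* The article sets no such reporting rule, and the sentence before the claim gives the ordinary conclusion about safety and effectiveness.
- *The trial is unsound without a sham arm.* An add-on comparison against lenses alone is a legitimate question.

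**Conclusion.** The point holds for the one sentence on specificity. This is not a matter of degree: the point-specific effect cannot be identified from these two arms at any sample size, and its share of an observed difference could be all, part or none. The size of the imbalance in treatment contact is 54 sessions against no matching sessions.

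The conclusion rests on the arms being as the article describes them, with no further arm in an unseen full protocol. The explicit statement that no sham group is included supports this. It does not rest on any assumption about how large the non-specific effects are, only on the design's inability to exclude them.

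The defect is an overclaim in interpretation. The randomized estimate of what is gained by adding the acupuncture course to lenses, and its planned analysis, are not affected by it.

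**What to change.** 1. Delete the specificity sentence from the closing paragraph of the Discussion.
2. State the conclusion the trial can support, in line with the aim under Study design. For example: *The trial estimates the effect of adding this acupuncture course to single-vision lenses, compared with single-vision lenses alone.*
3. Extend the existing no-sham limitation by one clause: *the effects of the chosen points are not separated from those of needling at any site, treatment contact and expectation.*

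There is no need to prescribe a single permitted wording for the primary conclusion; removing the overclaim and naming the contrast is enough. The arms, sample size, procedures and analysis stay as they are. The cost is a few lines of text and a narrower claim. Trial status reports six participants recruited, so the change can be made long before any result exists.
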